#### 2.2.3. Post-Intervention Evaluation

A final assessment will be performed one week after completion of the 16-week IST programme (week 17). All baseline measurements (physiological variables, functional capacity including MVIC and posture, quality of life by EQ-5D-5L, and the components of the sarcopenia diagnosis) will be repeated to assess any changes induced by the training, with the exception of the genetic analysis, which is only performed at baseline. Additionally, applicability questionnaires (safety, acceptance and perceived difficulty using Likert scales) [87] will be administered to assess the IST protocol.

### 2.3. Statistical Analysis

This study will employ a single-group design with pre- and post-intervention measurements. The analysis will follow an intention-to-treat (ITT) and, complementarily, per-protocol (PP) approach for participants with ≥90% session attendance. Missing data will be minimised through rigorous follow-up and promotion of retention (Section 2.1.3). The pattern and amount of missing data will be analysed; if <5% and MCAR (Missing Completely At Random), complete case analysis will be chosen for certain variables. For the main ITT analysis with larger missing data or with a specific pattern, multiple imputation techniques or mixed models (under the MAR—Missing At Random assumption) will be considered.

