#### 2.1.1. Criteria for Inclusion/Exclusion in Research

##### Sampling Method

Consecutive non-probabilistic sampling will be used. All individuals identified through the collaborating organisations who meet the eligibility criteria will be invited to participate until the target sample size (N = 18) is reached.

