##### Criteria for Discontinuation or Withdrawal of Participants During the Study

The IST progression protocol (Table 2) shall be applied in a standardised manner, with no individualised modifications to the progression. Persistent inability to follow the prescribed protocol, including unresolved mild discomfort, shall be managed by considering the following criteria for discontinuation or withdrawal:Voluntary withdrawal by the participant: Participants may withdraw at any time and for any reason, as informed in the consent, without penalty or impact on the participant’s medical care.Development or worsening of medical conditions: If, based on the medical judgement of the team or staff, a new condition or the worsening of a pre-existing condition contraindicates continuation with the IST or significantly increases the risk, participants may withdraw from the programme.Adverse events (AEs): Occurrence of a Serious Adverse Event (SAE) or persistent/considerable AE related to participation, which, based on the medical judgement of the principal investigator or study doctor, makes it inadvisable to continue. All these occurrences will be recorded and evaluated according to the safety protocol.Non-compliance with protocol:○Failure to complete a minimum of 90% of the sessions, even after considering the extension of the period.○Persistent inability or refusal to perform exercises according to instructions and proper technique, compromising safety or validity, despite supervision and correction.○Failure to complete scheduled assessments within 20 weeks.Significant lifestyle changes or concomitant treatments: Initiation of unrelated intense exercise, drastic unsupervised dietary changes, or medical treatments that significantly interact with outcomes or safety, as assessed by the research team.Failure to engage in follow-up sessions: If the participant becomes unresponsive and does not attend sessions/assessments, despite reasonable attempts at contact, discontinuation will be considered.

The main reason will be documented in all cases of discontinuation or withdrawal. Data collected up to that point will be securely retained and considered for inclusion in statistical analyses (e.g., intention-to-treat), as described in the ‘Statistical Analysis’ section. Participants who discontinue the intervention will be able to continue with scheduled assessments if they wish to do so, provided that this is feasible.

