#### 2.2.1. Study Outcome Variables (Outcomes)

The following variables will be assessed at pre- and post-intervention (week 0 and week 17, unless otherwise stated) to determine the efficacy and applicability of the IST, as distinguished from the eligibility measures (Section 2.1.1):A.Primary Outcome Variables (Assessment of reversal of dynapenia and sarcopenia):
1.Change in MVIC Knee Extensors:○Specific measurement variable: MVIC of the knee extensors, measured in Newtons (N) with the CIEX SYSTEM machine.○Analysis metric: Absolute change (MVIC_week17_–MVIC_week0_)○Method of aggregation: Mean and Standard Deviation (SD) of the change. The percentage change will also be calculated.○Time point(s): Baseline (week 0) and post-intervention (week 17) assessments.○Clinical Relevance: Knee extensor strength is key to functionality and independence in older adults; its improvement indicates reversal of dynapenia.2.Change at ASMMI:○Specific measurement variable: ASMMI (ASMM in kg/height^2^ in m^2^), measured by bioimpedance (InBody 230).○Analysis metric: Absolute change (ASMMI_week17_–ASMMI_week0_)○Method of aggregation: Mean and SD of change.○Time point(s): Baseline (week 0) and post-intervention (week 17) assessments.○Clinical Relevance: Fundamental diagnostic criterion for sarcopenia (EWGSOP2); an increase indicates improvement in the amount of muscle, essential for metabolic health and reduced frailty.
B.Secondary Outcome Variables

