#### 2.3.1. Sample Size Calculation

The sample size was determined after an internal pilot study (N = 50) conducted by the research team (Baigene), using a similar training protocol (CIEX SYSTEM machine) but without visual strength feedback. It was carried out in a population aged ≥65 years with and without sarcopenia/dynapenia and had a duration of 10 weeks. The primary variable for calculation was quadriceps MVIC (N). Pilot results (mean ± SD, Pre vs. Post):Left quadriceps: 224.78 ± 64.49 N vs. 296.55 ± 89.38 N; Cohen’s d (paired samples) = 1.22.Right quadriceps: 263.53 ± 84.66 N vs. 306.24 ± 106.74 N; Cohen’s d (paired samples) = 0.51. Effect sizes were calculated with the mean and SD of the pre-post differences. Given the expected greater improvement with feedback in this protocol, the more specific population (≥70 years with sarcopenia/dynapenia) and the longer duration of the current intervention, a (conservative) d = 0.80 was adopted for the calculation. With G*Power v3.1.9.7, for a related samples *t*-test, detecting d = 0.80 with 80% power and α = 0.05 (bilateral) requires N = 15. Adjusting for 15% losses, 18 participants will be recruited, an adequate number for this pilot exploratory study.

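### The main ITT analysis has only a MAR method for missing outcomes, which gives unmeasured stoppers roughly the gain of those measured; one baseline-anchored sensitivity analysis is needed

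*Protocol article*

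**What the plan says.** Protocol article, section 2.3, sets the analysis populations: "The analysis will follow an intention-to-treat (ITT) and, complementarily, per-protocol (PP) approach for participants with ≥90% session attendance". On missing data it says "if <5% and MCAR (Missing Completely At Random), complete case analysis will be chosen for certain variables". For the main ITT analysis with more missing data, or with a specific pattern, "multiple imputation techniques or mixed models (under the MAR—Missing At Random assumption) will be considered". No method that departs from MAR is named.

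Section 2.2.1 defines both primary outcomes (knee extensor MVIC and ASMMI) as the change from week 0 to week 17, with no assessment in between. Section 2.3.1 expects losses: "Adjusting for 15% losses, 18 participants will be recruited".

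The withdrawal criteria in section 2.1.2 include a serious or persistent related adverse event, a new or worsening condition, attendance below 90%, loss of contact, and "Persistent inability or refusal to perform exercises according to instructions and proper technique, compromising safety or validity, despite supervision and correction". The same section keeps the data of those who stop and lets them continue with assessments. Section 2.1.3 adds that they will be encouraged to attend at week 17 where feasible.

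**The concern.** In a single-arm pre-post design, the only people who can show what week 17 looks like are those measured at week 17. A MAR method predicts a missing week-17 value from what was observed. With two time points and no other variables named, that means the participant's baseline plus the average change of those measured, most of whom will have finished training. Someone who left because of a related adverse event, or because the exercises could not be done, is then treated as if the programme had worked for them about as well as for the others.

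What is at stake is how both primary results are read. Attendance below 90% is a withdrawal criterion and also the boundary of the per-protocol set, so those with week-17 data will largely be the per-protocol group. If the remaining ITT values are predicted from that group, close agreement between ITT and per-protocol is nearly built in and says little about whether drop-out mattered.

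**Working it through.** **The plan's own figures.** Section 2.3.1 states that "detecting d = 0.80 with 80% power and α = 0.05 (bilateral) requires N = 15". Exact noncentral-t power for a two-sided paired test at d = 0.80 is 0.790 with N = 14 and 0.821 with N = 15, so 15 is right. Allowing for losses, 15/0.85 = 17.65, rounded up to 18. The sample size reproduces and is not in question.

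**When the MAR branch applies.** One missing change score is 1/18 = 5.56%, which is above 5%. For a week-17 outcome the complete-case branch therefore applies only when nothing is missing. N would have to be at least 21 for one loss to fall below 5%. At the planned 15% rate, expected losses are 18 × 0.15 = 2.7. If losses are independent, the chance of none is 0.85^18 = 5.4%, so the MAR branch would apply in about 95% of cases.

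**Size of the shift.** Let g be the mean gain of those measured (here all finishers), k the number of stoppers without a week-17 value, and f the share of g that those stoppers really have. A MAR prediction from baseline returns about g for the whole group. The true mean over all 18 is g × [(18 − k) + k × f]/18, so the overstatement is 18/[(18 − k) + k × f] − 1.

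The illustration uses the pilot gains in section 2.3.1: left 296.55 − 224.78 = 71.77 N; right 306.24 − 263.53 = 42.71 N. The pilot had a different population and lasted 10 weeks, so these show scale only. The values of f are assumptions, since the document gives none. With k = 3:

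| f | All-18 mean as share of g | Overstatement | Left (MAR: 71.8 N) | Right (MAR: 42.7 N) |
|---|---|---|---|---|
| 1 (same as finishers) | 18/18 = 1.000 | 0% | 71.8 N | 42.7 N |
| 0.5 (half kept) | 16.5/18 = 0.917 | 9% | 65.8 N | 39.2 N |
| 0 (none kept) | 15/18 = 0.833 | 20% | 59.8 N | 35.6 N |
| below 0 (decline) | below 0.833 | above 20% | below 59.8 N | below 35.6 N |

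With f = 0 and fewer unmeasured stoppers, the overstatement is 18/17 − 1 = 5.9% for one and 18/16 − 1 = 12.5% for two.

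**Check by simulation.** The check used 20,000 trials of 18 with the left-quadriceps pilot means and SDs. The SD of the change was 71.77/1.22 = 58.8 N, which implies a pre-post correlation of 0.75. Three stoppers had zero true mean change and no week-17 value, and they were imputed by regression on baseline. The MAR estimate was 71.8 N, complete case also gave 71.8 N, and the true all-18 mean was 59.8 N. The equality of MAR and complete case holds because only baseline was used to impute.

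**The case against.** The strongest reply is that the article leaves room. MAR methods are only to be considered, no imputation model is fixed, and a sensitivity analysis is ordinary content for an analysis plan that is not shown. The point still concerns a method that the article states, because MAR is the only route it names for the main analysis. If the full analysis plan already holds an analysis that departs from MAR, the point is met.

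Second, a reader might infer that everyone who stops training is credited with the finishers' gain. The document does not support that. Sections 2.1.2 and 2.1.3 keep stoppers' data and seek a week-17 measurement. Those measured enter with their own values and also inform any imputation. Only people who stop and also go unmeasured are affected.

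Third, attendance, adverse events and session force are recorded during training. An imputation that used them could separate stoppers from finishers, and MAR would then not simply return the finishers' mean. This is a fair limit. But the plan does not name these variables, and no in-trial measure is described that could do the same for ASMMI.

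Fourth, zero gain is harsh for someone who leaves late or falls just short of 90% attendance. At the planning effect, the largest illustrated shift is 0.80 − 0.80 × 15/18 = 0.13 SD, while the 95% interval half-width with 15 measured is about 2.145/√15 = 0.55 SD. The shift is therefore modest beside sampling error. That limits the weight of the point. It does not remove the need to show the dependence on MAR.

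Fifth, the 5% threshold might be read as a source of bias. It is not: if it applies only when nothing is missing, complete-case analysis is then correct.

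**Conclusion.** The point holds in a limited form. The main ITT analysis rests on MAR alone, in a design where MAR from baseline gives unmeasured stoppers roughly the gain of those measured, and the protocol's own withdrawal reasons make that assumption doubtful. The ITT result would then largely repeat the per-protocol result.

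At 3 of 18 unmeasured stoppers, the overstatement of the mean gain runs from 0% through about 9% to 20%, and beyond 20% if stoppers decline. A reader might take 20% as the expected bias. The document does not support that, because the figure needs all three planned losses to be stoppers with no week-17 value and no gain. The range also assumes an imputation that does not use session force, attendance or adverse-event data. The point does not invalidate the trial and does not touch the sample size.

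**What to change.** Keep the MAR analysis as the main ITT analysis. State that it includes everyone who started IST and uses every week-17 value, including those taken after training stopped.

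Pre-specify one sensitivity analysis for both primary outcomes. It imputes participants who stopped and have no week-17 value around their own baseline, with no mean gain and with residual variability, so that the imputed values are not treated as known. Report the two analyses side by side, and describe the gain as robust to drop-out only if the confidence interval excludes zero in both.

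The cost is a few lines of text and one extra analysis, with no new data or participants. The downside is a possibly smaller estimate. With three no-gain stoppers, a standardised change of 0.80 falls to about 0.64 to 0.69, so the interval is more likely to include zero. Removing the complete-case branch is optional tidying and does not change the result.

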#### 2.3.1. Sample Size Calculation

The sample size was determined after an internal pilot study (N = 50) conducted by the research team (Baigene), using a similar training protocol (CIEX SYSTEM machine) but without visual strength feedback. It was carried out in a population aged ≥65 years with and without sarcopenia/dynapenia and had a duration of 10 weeks. The primary variable for calculation was quadriceps MVIC (N). Pilot results (mean ± SD, Pre vs. Post):Left quadriceps: 224.78 ± 64.49 N vs. 296.55 ± 89.38 N; Cohen’s d (paired samples) = 1.22.Right quadriceps: 263.53 ± 84.66 N vs. 306.24 ± 106.74 N; Cohen’s d (paired samples) = 0.51. Effect sizes were calculated with the mean and SD of the pre-post differences. Given the expected greater improvement with feedback in this protocol, the more specific population (≥70 years with sarcopenia/dynapenia) and the longer duration of the current intervention, a (conservative) d = 0.80 was adopted for the calculation. With G*Power v3.1.9.7, for a related samples *t*-test, detecting d = 0.80 with 80% power and α = 0.05 (bilateral) requires N = 15. Adjusting for 15% losses, 18 participants will be recruited, an adequate number for this pilot exploratory study.

#### 2.3.2. Analysis Strategy

Primary and secondary quantitative variables will be compared pre-post with Student’s *t*-tests for related samples, after testing for normality (Shapiro-Wilk). If the data are not normally distributed or contain outliers, non-parametric tests (e.g., the Wilcoxon signed-rank test) will be employed. Effect sizes (Cohen’s d) and confidence intervals will be calculated. Multivariate analyses will include a multiple linear regression to explore the influence of genetic and environmental variables on strength and muscle mass improvement, with Bonferroni correction for genetic analyses. Qualitative variables (e.g., sarcopenia diagnosis) will be analysed by using McNemar tests. Applicability variables (Likert scales, adverse events) will be analysed with descriptive statistics and *t*-tests or Wilcoxon tests for pre-post comparisons on Likert scales. Additionally, exploratory subgroup analyses will be performed to assess whether the response to IST on primary variables differs according to sex, age ranges (70–79 vs. ≥80 years) and baseline severity of sarcopenia/dynapenia. Adjustment for baseline covariates will be considered in regression models. The software will be IBM SPSS v29.0 and R v4.3.1.

For the assessment of the secondary hypotheses concerning the applicability (Section 2.2.2) of the IST protocol, specific analyses will be carried out:

Hypothesis H1 (low injury risk): This will be assessed through two approaches. First, Adverse Events (AEs) will be recorded (including their type, severity, and causality), and ‘low risk’ will be inferred if the incidence of IST-related injuries is minimal and comparable to or lower than rates reported in the literature for strength training in older adults [1,33,34,35]. Second, Perceived Safety will be measured post-intervention using a 5-point Likert scale; the approach for this subjective scale is based on similar methods used in previous research [87]. The hypothesis will be supported by a mean score of ≥4.

Hypothesis H2 (high acceptance): This will be assessed by: (1) compliance rate, with a success threshold of ≥90% of completed sessions, and (2) a satisfaction score from a 5-point Likert scale administered post-intervention, using a validated measurement approach [88]. The hypothesis will be supported by a mean satisfaction score of ≥4.

Hypothesis H3 (low perceived difficulty): This will be assessed using a 5-point Likert scale for perceived technical difficulty post-intervention, based on validated methods [89]. The hypothesis will be supported by a mean score of ≤2.

Hypothesis H4 (Genetic influence). The association between polymorphisms (muscle typology [63,64], inflammation [70,71], tissue regeneration [72,73], energy metabolism [74,75,76]) and improvements in mass/strength (IST) will be analysed by multiple linear regression, adjusting for covariates and with the Bonferroni correction test.

For the Likert-based outcomes (H1–H3), the magnitude of change will also be assessed by calculating Cohen’s d.

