#### 2.1.4. Data Management

The following plans will be implemented for the data management of the study:Standardised Case Report Forms (CRFs): Standardised (physical or digital) CRFs, designed specifically for this study, will be used for all variables. These CRFs will be available for ethical or audit consultation if necessary.Data Entry: Data from physical CRFs will be entered into a Microsoft Excel database. To ensure data quality, a second team member will thoroughly double-check all entered data against the original forms.Data Coding: Variables will be coded according to a pre-established data dictionary to ensure consistency. Personally identifiable data will be excluded from the analysis database, using anonymised participant identification codes instead.Data Quality: In addition to input verification, range and logical consistency checks will be performed to identify errors or outliers. Any inconsistencies will be reviewed and corrected in consultation with the original CRFs or measurement staff. Periodic data quality reviews shall be performed.Data Security and Storage: All data (physical forms and electronic database) will be stored securely. Electronic data will be stored in password-protected institutional computers, with access restricted to the principal investigator’s team. Regular encrypted backups will be performed and placed in a secure, locked external hard drive. Paper forms and informed consents will be stored under lock and key at Baigene S.L. In compliance with institutional regulations, good research practice, the EU General Data Protection Regulation (GDPR) and applicable Spanish legislation, all study data will be securely stored for a minimum of 15 years following the completion of the trial.

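### The test for both primary outcomes is chosen from the data by Shapiro-Wilk or an undefined outlier trigger, although the metric is mean change and the trial is sized for the paired t-test

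*Protocol article*

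**What the plan says.** Section 2.3.2 (Analysis Strategy) sets one rule for all quantitative outcomes: "Primary and secondary quantitative variables will be compared pre-post with" Student's t-tests "for related samples, after testing for normality (Shapiro-Wilk"). It continues: "If the data are not normally distributed or contain outliers, non-parametric tests (e.g., the Wilcoxon signed-rank test) will be employed". The abstract repeats the same either/or for the main analyses.

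Section 2.2.1 defines both primary outcomes as the absolute change from week 0 to week 17. The summary is "Mean and Standard Deviation (SD) of the change" for knee extensor MVIC and "Mean and SD of change" for ASMMI.

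Section 2.3.1 sizes the trial for a related-samples t-test only: "a (conservative) d = 0.80 was adopted for the calculation", and "detecting d = 0.80 with 80% power and α = 0.05 (bilateral) requires N = 15".

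The only other mention of outliers is in Section 2.1.4 (Data Management), where "range and logical consistency checks will be performed to identify errors or outliers". That is a cleaning step and gives no numerical criterion for choosing a test. Nowhere does the article name one primary test or give the non-parametric test the role of a sensitivity analysis.

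**The concern.** Three features of the rule cause trouble together.

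- **The quantity tested can change.** The t-test addresses the mean change, which is the declared metric. The signed-rank test addresses the pseudo-median of the differences (or their symmetry about zero). The two agree when differences are symmetric. When they are skewed, which is one of the situations that triggers the switch, the p-value no longer belongs to the mean change and Cohen's d printed next to it.
- **One trigger is open.** Without an outlier rule, two analysts who both follow Section 2.3.2 can reach different primary tests on the same data. Naming the fallback only as an example adds to this. Section 2.1.5 makes analysis by someone outside data collection, or analysis without the time coding, conditional on feasibility, so the judgement may be made with results in view.
- **The design basis is the t-test.** The effect size, the power and N = 15 all refer to it.

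At stake are the reproducibility of the two primary p-values and, to a small degree, their error rate.

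**Working it through.** **1. The plan's own figure.** Inputs from Section 2.3.1: d = 0.80, two-sided α = 0.05, 80% power, 15% losses. Power of the paired t-test is P(|T| > t(0.975, n−1)), where T is noncentral t with n−1 df and noncentrality d√n.

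- n = 14: power 79.0%.
- n = 15: noncentrality 0.80 × √15 = 3.10, power 82.1%. N = 15 reproduces.
- Losses: 15/0.85 = 17.6, so 18. This reproduces too.

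**2. How often the rule would switch.** The article gives neither a Shapiro-Wilk level nor an outlier rule. Assumed here: level 0.05, any point beyond 1.5 × IQR from the quartiles, both applied to the paired differences. With normal differences and 10,000 simulated trials per case:

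| n | Shapiro-Wilk alone | Shapiro-Wilk or outlier |
|---|---|---|
| 15 | 4.8% | 30.4% |
| 18 | 5.0% | 31.9% |

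Almost all the switching in normal data comes from the outlier trigger, the part with no definition.

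**3. Type I error for the hypothesis of zero mean change.** Same assumptions. The simulation standard error is about 0.2 points for the normal rows and up to about 0.3 for the skewed rows.

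| Differences (true mean 0) | n | t-test | Switching rule | Excess (points) |
|---|---|---|---|---|
| Normal | 15 | 4.7% | 5.0% | 0.3 |
| Normal | 18 | 5.2% | 5.5% | 0.3 |
| Lognormal, σ = 0.5 | 15 | 7.2% | 8.8% | 1.6 |
| Lognormal, σ = 0.5 | 18 | 7.2% | 9.7% | 2.5 |
| Exponential (skewness 2) | 15 | 8.9% | 11.4% | 2.5 |
| Exponential (skewness 2) | 18 | 8.1% | 12.0% | 3.8 |

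For skewness 1 at n = 15, separate runs give 6.2–6.3% for the t-test and 7.0–7.2% for the switch, an excess of roughly 0.7 to 1 point. With normal differences, taking whichever of the two tests is significant gives 5.3% (n = 15) and 5.9% (n = 18). That bounds what free choice between these two tests could do there.

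**4. How much of the excess over 5% belongs to the t-test.** Exponential case, n = 15: (8.9 − 5)/(11.4 − 5) = 3.9/6.4, about 61%. At n = 18: (8.1 − 5)/(12.0 − 5) = 3.1/7.0, about 44%. Fixing the t-test therefore removes only part of the inflation under strong skew.

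**5. Power at d = 0.80, n = 15.** Normal differences: t-test 82.1%, Wilcoxon 80.2%, switch 82.6%. Heavy-tailed differences (t with 4 df): t-test about 0.85, against 0.88–0.89 for Wilcoxon or the switch.

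**6. The alternative of fixing Wilcoxon.** Its efficiency relative to the t-test under normality is 0.955, so 15/0.955 = 15.7, or 16 evaluable. Then 16/0.85 = 18.8, or 19 recruited.

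**The case against.** The strongest reply is that the rule is written in advance: it names a default test, a check and a fallback, and the pattern is widely used. A condensed article may leave the outlier cut-off and the Shapiro-Wilk level to an analysis plan that is not shown. That is fair for the missing numbers alone. It does not answer the point that the article itself lets the data choose the primary test while its metric and sample size are tied to one of the two.

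A reader might infer that normality will be checked on the pre and post values and not on the differences. The document does not say that. It speaks only of the data, and the surrounding sections work with differences, so this reading should not be held against the plan.

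A reader might also infer serious inflation of type I error. The larger figures need differences that are strongly skewed yet have mean exactly zero, and nothing in the document suggests this for MVIC or ASMMI. If pre and post values are exchangeable under no effect, the differences are symmetric about zero. Simulations of that case (lognormal values, σ = 0.5 and 1) gave 4.8% to 5.2% for the switching rule at n = 15 and 18, even though switching was frequent.

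It also stands that the 30% switching rate rests on an outlier rule that the protocol does not state, that the t-test is itself above 5% under skew, and that the mean and SD of the change will be reported whichever test is used.

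**Conclusion.** The point holds as a minor one. Section 2.3.2 fixes the primary test badly: Shapiro-Wilk or an undefined outlier trigger can replace the t-test for both primary outcomes, and the replacement is named only by example. This conflicts with a mean-change metric and a sample size built on the paired t-test.

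The numerical harm is small. The excess in type I error over the t-test is about 0.3 to 1 point for symmetric or mildly skewed differences, and about 2 to 4 points under a strongly skewed mean-zero null. These sizes depend on the assumed 0.05 pre-test level, the 1.5-IQR rule and the chosen distributions. The textual defect, an open trigger and a test that may not match the reported estimate, does not depend on them. N = 15 evaluable and 18 recruited are correct for the stated inputs. The trial is single-arm and exploratory, which further limits the consequence.

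**What to change.** In Section 2.3.2, name the paired t-test on the week-17 minus week-0 difference, with its 95% CI, as the single primary test for both MVIC and ASMMI, whatever Shapiro-Wilk or outlier checks show. Report the Wilcoxon signed-rank test on the same differences as a pre-specified sensitivity analysis. Values that pass the data checks in Section 2.1.4 stay in the analysis.

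The cost is one sentence and no participants. The downside is about 4 points of power if differences are heavy-tailed (about 0.85 against 0.88–0.89 for t with 4 df at d = 0.80, n = 15). If the team prefers Wilcoxon as the fixed test, the trial should be sized for it, at about 16 evaluable and 19 recruited, and the reported estimate should match that test.

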## 4. Limitations and Strengths of the Study

The results will depend on the comparison between initial and final assessments, and it is crucial that the subjects maintain similar physical and psychological conditions. Working with a vulnerable population may limit the collection of completely objective data despite their actual evolution.

A significant methodological limitation is the absence of a parallel control group. The current single-arm design was chosen for this initial phase to assess the feasibility and preliminary effects of the IST protocol before proceeding to a larger-scale Randomised Controlled Trial (RCT). This feature compromises internal validity, making it difficult to attribute changes to the IST alone with any degree of certainty; factors such as natural progression of the condition, Hawthorne effects or uncontrolled variables may play a role. The inclusion of a control group, preferably through an RCT, as a strategy for future research would strengthen the ability to establish a direct causal relationship and improve internal validity.

Another limitation that may affect internal validity is the exhaustive control and quantification of lifestyle variables (diet, spontaneous physical activity) and medication changes unrelated to the intervention. Although general data are collected (in comprehensive geriatric assessment and for genetic analysis) and participants are instructed to maintain their habits (Section 2.1.3), the absence of detailed baseline assessment and continuous monitoring of these factors limits the ability to completely rule out their role as confounders. In order to partially mitigate this, an analysis of covariance (ANCOVA) could be employed to adjust the results for certain variables, provided they are reliably measured and significant changes are recorded. Future studies would benefit from more rigorous experimental control or more detailed measurement of these confounders.

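### Section 2.3.2 names plain Cohen's d for 15 to 18 pairs; reporting the bias-corrected form would remove an average overstatement of about 5% at no cost

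*Protocol article*

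**What the plan says.** Section 2.3.2 compares quantitative outcomes before and after training with the paired t-test, or with the Wilcoxon signed-rank test when data are non-normal or contain outliers. It then adds: "Effect sizes (Cohen’s d) and confidence intervals will be calculated". For the Likert outcomes it says that "the magnitude of change will also be assessed by calculating Cohen’s d". Neither sentence states a standardiser or a small-sample correction.

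The only definition of d is in Section 2.3.1, for the earlier internal pilot of 50 people: "Effect sizes were calculated with the mean and SD of the pre-post differences". The same section fixes the size of the present trial: "detecting d = 0.80 with 80% power and α = 0.05 (bilateral) requires N = 15", and then "Adjusting for 15% losses, 18 participants will be recruited, an adequate number for this pilot exploratory study".

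Standardised effects are not the main summary. For knee-extensor MVIC, Section 2.2.1 asks for "Mean and Standard Deviation (SD) of the change. The percentage change will also be calculated", and for ASMMI it asks for the mean and SD of the change. Section 4 describes the aim of this phase as "to assess the feasibility and preliminary effects of the IST protocol before proceeding to a larger-scale Randomised Controlled Trial (RCT".

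**The concern.** The sample d divides by an estimated SD. With few pairs, the reciprocal of that SD is on average too large, so d is biased upward. The bias depends only on the degrees of freedom and fades as the sample grows. It is about 1.6% at 50 pairs, the size of the internal pilot, but about three to four times that at 15 to 18 pairs.

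The ordinary meaning of Cohen's d is the uncorrected form, because the corrected form has its own name, Hedges' g. The accuracy of the standardised effects that this small trial will publish is at stake. A confidence interval shows random error, but it does not remove an average upward shift in the point estimate.

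**Working it through.** **Inputs.** Design effect d = 0.80, two-sided α = 0.05, 80% power, 15 evaluable pairs, 15% losses, 18 recruited (all Section 2.3.1). Assumptions: d is the mean change over the SD of the changes, and the changes are normal.

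**1. The plan's own figure.** Paired t-test power comes from the noncentral t with n − 1 degrees of freedom and noncentrality d√n. It is 0.790 at n = 14 and 0.821 at n = 15, so 15 is the smallest n that reaches 80%. Then 15 / 0.85 = 17.6, rounded up to 18. The protocol's figures reproduce. Analysed pairs should therefore lie between about 15 (df = 14) and 18 (df = 17).

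**2. Bias of the plain paired d.** With true value δ, E[d] = δ / J, where J = Γ(df/2) / [√(df/2) · Γ((df − 1)/2)], approximately 1 − 3/(4df − 1).

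| Pairs | df | J | Overstatement, 1/J − 1 | E[d] at δ = 0.80 | Bias |
|---|---|---|---|---|---|
| 15 | 14 | 0.945 | 5.8% | 0.846 | 0.046 |
| 18 | 17 | 0.955 | 4.7% | 0.838 | 0.038 |

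A simulation of 400,000 trials at each n gave 5.9% and 4.7%.

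**3. Bias against random error.** Var(d) = [df/(df − 2)] · (1 + nδ²)/n − δ²/J². At δ = 0.80:
- n = 15: (14/12)(10.6/15) − 0.64/0.8936 = 0.824 − 0.716 = 0.108, so the SD is 0.33 and bias/SD is 0.14.
- n = 18: (17/15)(12.52/18) − 0.64/0.9122 = 0.788 − 0.702 = 0.087, so the SD is 0.29 and bias/SD is 0.13.

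An observed d of 0.80 has a noncentral-t 95% interval of 0.20 to 1.37 (n = 15) or 0.26 to 1.32 (n = 18).

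**4. Effect of the correction.** g = J · d is unbiased and has variance J² · Var(d). At δ = 0.80 the mean squared error falls from 0.110 to 0.097 (about 12%) at n = 15, and from 0.088 to 0.079 (about 10%) at n = 18. The corrected estimate is therefore less biased and also less variable. An observed d of 0.80 would be reported as g = 0.945 × 0.80 = 0.76 at both sample sizes, to two decimals.

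**The case against.** The strongest reply is that Section 2.3.2 contains no false statement. It does not say that d will be left uncorrected, and the standardiser, the correction and the interval method are often left to a statistical analysis plan, which is not available here. That stands as a limit: the size above depends on reading Cohen's d in its ordinary sense. It is also fair that the bias is small beside the random error and that confidence intervals are already planned.

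Three stronger readings are tempting, and the protocol supports none of them.

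- *That d is the figure passed on to the later randomised trial.* Section 4 speaks only of preliminary effects and does not say that d will size that trial. A within-group pre-post d is also not the between-group effect that such a trial needs. Section 4 already names the missing control group as a limitation, and a factor of 0.95 does nothing about that.
- *That a later trial would be 9 to 11% too small.* That range is 1 − J² (8.8% at n = 18, 10.6% at n = 15). It puts the mean of d into a sample size proportional to 1/d². The function is convex and d is right-skewed, so the result describes neither the average nor the typical later trial. The median d is only about 2% high, which corresponds to a shortfall of about 3 to 4%.
- *That every reported effect is inflated.* The bias is in the mean. At δ = 0.80, d falls below the true value in about 48% of trials.

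A last objection also stands. The correction factor and the noncentral-t interval assume normal differences, so they should not be applied to outcomes that Section 2.3.2 moves to the Wilcoxon test.

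**Conclusion.** The point holds as a minor improvement in reporting. With 15 to 18 analysed pairs, the plain paired d exceeds the true standardised effect by 4.7 to 5.8% on average, about one seventh of its sampling SD when the true effect is 0.80. This rests on three assumptions: d is standardised by the SD of the changes as in Section 2.3.1, the differences are normal, and no correction is specified elsewhere. P-values, the decision rules for the hypotheses and the primary mean changes in N and kg/m² do not depend on it. It is not an error in the plan, and nothing in the protocol shows that it would carry over into the later trial.

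**What to change.** In Section 2.3.2, replace the sentence on effect sizes with wording to this effect: for pre-post outcomes analysed by the paired t-test, the bias-corrected standardised mean change (Hedges' g, using the SD of the differences and the factor J for the analysed n) will be reported with a noncentral-t 95% confidence interval, next to the raw mean change; for outcomes analysed by the Wilcoxon signed-rank test, an effect size matched to that test, such as the matched-pairs rank-biserial correlation, will be reported.

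This also states the standardiser for the trial's own results, which at present is given only for the earlier pilot. The change covers outcomes measured both before and after training. Section 2.2.1 lists the Likert scales at week 17 only, so this wording does not apply to them.

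The cost is one sentence and no new data. Reported standardised effects become about 5% smaller.
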